## Abstract

**Background:**

Innovative analyses of cardiovascular (CV) risk markers and health behaviors linked to neighborhood stressors are essential to further elucidate the mechanisms by which adverse neighborhood social conditions lead to poor CV outcomes. We propose to objectively measure physical activity (PA), sedentary behavior, and neighborhood stress using accelerometers, GPS, and real-time perceived ecological momentary assessment via smartphone apps and to link these to biological measures in a sample of White and African American women in Washington, DC, neighborhoods.

**Objective:**

The primary aim of this study is to test the hypothesis that living in adverse neighborhood social conditions is associated with higher stress-related neural activity among 60 healthy women living in high or low socioeconomic status neighborhoods in Washington, DC. Sub-aim 1 of this study is to test the hypothesis that the association is moderated by objectively measured PA using an accelerometer. A secondary objective is to test the hypothesis that residing in adverse neighborhood social environment conditions is related to differences in vascular function. Sub-aim 2 of this study is to test the hypothesis that the association is moderated by objectively measured PA. The third aim of this study is to test the hypothesis that adverse neighborhood social environment conditions are related to differences in immune system activation.

**Methods:**

The proposed study will be cross-sectional, with a sample of at least 60 women (30 healthy White women and 30 healthy Black women) from Wards 3 and 5 in Washington, DC. A sample of the women (n=30) will be recruited from high-income areas in Ward 3 from census tracts within a 15% of Ward 3’s range for median household income. The other participants (n=30) will be recruited from low-income areas in Wards 5 from census tracts within a 15% of Ward 5’s range for median household income. Finally, participants from Wards 3 and 5 will be matched based on age, race, and BMI. Participants will wear a GPS unit and accelerometer and report their stress and mood in real time using a smartphone. We will then examine the associations between GPS-derived neighborhood variables, stress-related neural activity measures, and adverse biological markers.

**Results:**

The National Institutes of Health Institutional Review Board has approved this study. Recruitment will begin in the summer of 2021.

**Conclusions:**

Findings from this research could inform the development of multilevel behavioral interventions and policies to better manage environmental factors that promote immune system activation or psychosocial stress while concurrently working to increase PA, thereby influencing CV health.

**International Registered Report Identifier (IRRID):**

PRR1-10.2196/29191

## Introduction

### Background

Promoting physical activity (PA) is a critical public health goal because insufficient PA participation affects all age groups and various racial and ethnic groups in the United States (US) [1]. Approximately 10% of deaths are attributed to insufficient PA in the US [2], and engaging in regular PA (ie, meeting the PA guidelines of at least 150 min/week of at least moderate intensity PA) can reduce the risk of numerous chronic diseases (eg, cardiovascular disease [CVD]) [3]. Furthermore, in 2018, the newly released Physical Activity Guidelines for Americans, 2nd edition documented that regular PA has immediate health benefits, including lowering blood pressure, increasing sleep quality, decreasing anxiety, and improving cognitive function and insulin sensitivity [4]. Despite the well-demonstrated PA benefits, most US adults do not engage in sufficient PA, when measured by accelerometers [5,6]. In particular, African American adults have a lower PA level than their White counterparts, with 7.7% of African American adults and 8.2% of White adults meeting the PA guidelines [6].

The application of a multilevel social-ecological framework to determine changes in the environment and policy that would promote PA participation has been supported by authoritative US health institutions and international organizations over the past two decades [7-9]. This conceptual framework identifies relevant factors at multiple levels, ranging from genetic, intrapersonal, interpersonal, social, and cultural, to environmental factors [10]. The key principle of the social-ecological model posits that each level can impact behavior, and individuals can impact and are influenced by their environment, particularly when considering psychosocial effects [11]. Recent interventions are increasingly focusing on the role that the neighborhood social environment (eg, poverty, social disorder, and crime [12]) may play as a source of stressors that shape low levels of PA at the population level [8,13].

Although the neighborhood social environment is an important factor in promoting PA [13], a key limitation in neighborhood social environment research is that the majority of such research systematically focuses on residential areas (ie, home) when investigating relationships between objectively measured environmental exposures via geographic information system (GIS) and PA [13]. However, individuals are generally mobile and engage in daily activities that are not restricted to places close to residential areas (eg, workplace) [14]. This generates a geospatial mismatch between exposures to the neighborhood social environment and locations where health behaviors occur [13,15,16]. Previous studies have also used self-reported PA, resulting in potential recall and social desirability bias [17].

When coupled with the neighborhood social environment as a source of stressors, psychosocial factors, such as chronic stress and depression, have an inverse relationship with PA and ultimately CVD [18]. Furthermore, a recent study in adults without CVD and our research in African American women in Washington, DC, demonstrated that amygdala activity (ie, chronic stress–related neural activity) assessed via 18-fluorodeoxyglucose (FDG) positron emission tomography-computed tomography (PET/CT) were significantly associated with subsequent CVD events [19] and vascular inflammation, a subclinical marker of atherosclerosis [20,21]. In addition, another recent study showed that neighborhood-level socioeconomic status (SES) was inversely associated with amygdala activity and arterial inflammation [22]. These findings are important for validating the relationship between chronic stress because of neighborhood factors and CVD events. However, the major limitations of the previous study were that they did not account for individual-level SES in the analytic models. Instead, they used neighborhood-level SES as a proxy for individual-level SES and examined the associations between neighborhood SES and amygdala activity. Furthermore, participants were chosen from a clinical database, which was not representative of the general US adults, and they were predominantly White adults [22]. Further research is needed to elucidate the associations between psychosocial factors, amygdala activity, and biological markers of adverse cardiac events in diverse populations and to assess both individual- and neighborhood-level SES.

### Objectives

To address these limitations, researchers have increasingly used an objective PA monitor (ie, accelerometer) linked to data from GPS units to track locations where PA occurs [23,24]. GPS units are often used to quantify an individual’s daily activity space (ie, defined as locations where individuals travel or move throughout the day) [23-28]. Ecological momentary assessment (EMA) also helps researchers to better understand psychosocial factors (eg, stressors and mood) in real time and psychosocial-environment contexts for health behaviors [29], such as PA and sedentary behavior. Therefore, the simultaneous use of three distinct methods (accelerometer, GPS, and EMA) reduces recall bias and the geospatial mismatch between exposures to the neighborhood social environment and PA [13]. In our study, we plan to measure both individual- and neighborhood-level SES among a diverse sample of adult women.

This pilot research will address current gaps in understanding the determinants of health disparities for populations from both high- and low-SES neighborhoods in Washington, DC, by applying geospatial tools and methods (ie, accelerometer, GPS, and EMA) and by linking to biomarkers of stressors. This research is innovative because it will apply geospatial tools and methods for tracking individual daily mobility and examine their linkage with biological measures, integration of neighborhood social measures for more comprehensive and objective assessment of factors that may lead to stress-related neural activity and poor CV outcomes. Therefore, the aims of this pilot study are as follows:

Aim 1: To test the hypothesis that living in adverse neighborhood social environment conditions is associated with higher stress-related neural activity among 60 healthy women living in high- or low-SES areas in Washington, DC.

Sub-aim 1: To test the hypothesis that the association is moderated by objectively measured PA via an accelerometer and psychosocial factors via EMA.

Aim 2: To test the hypothesis that residing in adverse neighborhood social environment conditions is related to differences in vascular function.

Sub-aim 2: To test the hypothesis that the association is moderated by objectively measured PA and psychosocial factors via EMA.

Aim 3: To test the hypothesis that adverse neighborhood social environment conditions are related to differences in immune system activation.

### Implications

This geospatial pilot study has a strong impact because the associations between neighborhood social contexts and stress-related neural activity (ie, marker of chronic stress–related neural activity) are highly understudied. This study is also novel because the linkages between neighborhood factors, detailed immune markers related to amygdala activity, and vascular function are limited. In addition, this geospatial pilot study will be among the first to include innovative geospatial technologies and tools to further characterize exposure to adverse neighborhood contexts within an individual’s daily mobility and link these data to an individual’s stress and mood through EMA data. Findings from this research could accelerate the development of multilevel behavioral interventions and environmental policies to better manage environmental factors that promote psychosocial stress or interventions that increase PA, which in turn can promote cardiovascular health.

## Methods

### Study Design

This is a cross-sectional study designed to investigate the impact of neighborhood environment on cardiovascular health and PA in African American and White women residing in Washington, DC, neighborhoods. Study participants will first visit the National Institutes of Health (NIH) Clinical Center where baseline health information will be collected and three devices will be distributed (accelerometer, GPS, and EMA app; Figure 1). After 14 days, participants will return to the Clinical Center for a final blood draw and cardiovascular examination. The NIH Institutional Review Board (IRB) approved this study, and this study has been registered on ClinicalTrial.gov (NCT04014348).

**Figure 1 figure1:**
[figure not shown]
Flowchart of events.

### Study Participants

A sample of women (at least n=30; 15 White women and 15 African American women) will be recruited from higher SES census tracts within a 15% range of the median household income in Ward 3 (median household income=US $126,184) [30]. The other participants (at least n=30; 15 White women and 15 African American women) will be recruited from lower SES census tracts within a 15% range of the median household income in Ward 5 (median household income=US $68,375) [31]. Participants from Wards 3 and 5 will be matched based on age, race, and BMI.

### Eligibility

Individuals eligible for this protocol will meet the following inclusion criteria: (1) a healthy White female or healthy Black female of African descent; (2) must be aged between 19 and 45 years; (3) must not have any chronic health condition, including lung disease or active infection; (4) must be living in Washington, DC, Wards 3 or 5; (5) must have access to a smartphone; (6) must be able to provide informed consent; and (7) must speak English. Individuals who meet the following criteria will be excluded from this study: (1) pregnant or breastfeeding; (2) physically unable to perform PA for any reason; (3) weight changes greater than 20% over the past 3 months; (4) obesity (measured BMI≥30.0 kg/m^2^); (5) high or low blood pressure; (6) diabetes; (7) history of mental illnesses, treated with medication and therapy; (8) history or evidence of hyper or hypothyroidism; (9) current medication use for chronic illness; (10) HIV; and (11) food allergies or highly restrictive diets that may prevent the ability to consume a controlled metabolic diet.

### Recruitment

Recruitment strategies include (1) distribution of recruitment flyers targeting potential participants in public locations throughout Wards 3 and 5, concentrating on areas in or near the targeted census tracts; (2) inclusion of study information on ClinicalTrials.gov, NIH Search the Studies, and a dedicated recruitment website on the Clinical Center Office of Patient Recruitment website (Current Protocols area); (3) use of ResearchMatch. for identification of healthy volunteers meeting criteria; (4) use of NIH (National Heart, Lung, and Blood Institute [NHLBI]/Clinical Center) social media accounts—Facebook, Twitter, and Craigslist with IRB-approved messages; and (5) distribution of recruitment messages on NIH listservs. This study was approved by the NIH Intramural IRB (NCT 04014348). Before enrollment in this study, our trained research staff will obtain written informed consent from all participants.

### Devices

Participants will receive an accelerometer (ie, objective activity monitor; ActiGraph wGT3X-BT) to measure PA, sedentary time, and sleep duration for at least 14 days. The ActiGraph accelerometer has been previously used to objectively assess PA [23,24], sedentary time [23,24], and sleep duration [32] among adults. The data will be collected at 1-minute epochs. Two distinct cut-points based on approaches by Troiano [5] and Matthews [33] will be used to determine the intensity of PA. Participants will be instructed to wear the monitor on their dominant wrist with a wristband at all times, except when bathing or swimming. A valid day of accelerometer monitoring is defined as ≥10 hours of wear time [33]. The time-stamped recordings from the accelerometers will be linked with GPS data.

Participants will also receive a GPS unit (ie, tracking device, Qstarz BT-Q1000eX GPS Logger). The GPS unit receives a satellite signal to identify latitude and longitude coordinates for a given period. GPS units will monitor participants’ daily activities via locations where they travel throughout the day for at least 14 monitoring days. GPS units will also record distance, speed, elevation, and time. The data will be collected at 1-minute intervals. This device has been used successfully in a recent study [34]. This GPS device is small and can be worn on a belt or placed in a backpack or bag. It will provide a timestamp and GPS coordinates. A valid day of GPS tracking is defined as ≥10 hours of wear time [35].

We will use a smartphone app to record EMA data via a mobile phone; these methods have been previously used for adults [36,37]. We will use two approaches for participants to record their PA, neighborhood environment, and stress. The first is an event contingency assessment. With this assessment, participants will be expected to record within the smartphone app when they engage in a certain behavior (eg, PA) within 15 minutes of the event occurring. The other type of assessment involves random survey prompts. Participants will respond to a series of questions on each day of the week. They will receive EMA random prompts for each assessment for that day (up to three random prompts for each assessment [morning, afternoon, and evening] and a maximum of nine prompts each day). The survey may take approximately 2-3 minutes to complete each time. Each item assesses the type of neighborhood context for the physical environment (eg, home, work, and outdoor), vegetation (amount of trees), traffic (amount of traffic), and safety (feeling safe and violence). Mood (positive and negative affect) and stressors (eg, daily hassles) from the EMA survey will be used specifically as psychosocial factors for each sub-aim. Previously validated EMA surveys and protocols for adults will be used in the proposed study [36,37].

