### Lessons Learned From Feasibility of GPS Use

When 11 participants from our study (ClinicalTrials.gov identifier NCT03288207) returned the GPS units to research staff members, GPS tracking was generally accepted. Pilot device testing revealed several concerns that will be addressed in this study. For instance, participants mentioned that they often forgot to charge the GPS device each night, as required by their limited battery life. They also sometimes forgot to bring the GPS with them when they left the house each morning.

For the overall study, we plan to address these device issues using the EMA app. The morning EMA prompt will include a message reminding participants to bring all of their devices, and the evening prompt will include a message reminding participants to charge their GPS units. These messages will hopefully curtail user errors and increase device compliance.

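### The 10-hour valid-day rule for the accelerometer is not limited to waking wear, so a day with only one to three waking hours observed can enter the PA measures

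*Protocol article*

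**What the plan says.** The Devices section of the protocol article sets three things for the accelerometer.

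- Purpose: the device is given out "to measure PA, sedentary time, and sleep duration for at least 14 days".
- Wear: participants are told to "wear the monitor on their dominant wrist with a wristband at all times, except when bathing or swimming".
- Validity: "A valid day of accelerometer monitoring is defined as ≥10 hours of wear time".

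Table 2 builds the PA moderators from these recordings, among them daily mean MVPA minutes and total PA minutes. Under Statistical Analysis, PA is named as an example of a health-related covariate for aim 1, and aims 2 and 3 take over the same covariates. PA is also the moderator in both sub-aims, and it is cut at its mean into high and low if the interaction is significant.

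For the GPS logger, the Devices section sets the same threshold: "A valid day of GPS tracking is defined as ≥10 hours of wear time". It also says: "This GPS device is small and can be worn on a belt or placed in a backpack or bag". The feasibility section on GPS use reports of the 11 test participants: "They also sometimes forgot to bring the GPS with them when they left the house each morning". It adds that "they often forgot to charge the GPS device each night, as required by their limited battery life".

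**The concern.** A ten-hour minimum is meant to ensure that enough of the active day was seen for a daily PA total to mean something. It does so if the hours counted are waking hours. Here the monitor is to be worn through the night, and the stated rule counts wear without restricting it to waking time. Most of the ten hours can then be sleep, and the day's MVPA, total PA and sedentary minutes may come from a small part of the waking day.

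What is at stake is the PA variable that appears in every aim. If all women were affected in equal proportion, their ranking and the split at the mean would hardly change. The harm comes when the share of thinly observed days differs between women. A woman who often takes the monitor off by day then looks inactive because she was not observed, and she may fall into the low-PA stratum.

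The GPS rule has a related but smaller weakness. A logger in a bag has no wear sensor described, and nothing in the definition tells a carried unit from one left at home.

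**Working it through.** The plan gives no figure that depends on the valid-day rule, so there is nothing to reproduce. The check asks how little of the waking day the rule can accept, and what that could do to a daily mean.

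**Inputs**
- Threshold: 10 hours of wear, any time of day (Devices).
- Sleep per night, s: 7, 8 or 9 hours. Assumed; not in the documents.
- Share of valid days at the bare minimum, f: 5% to 30%. Assumed; not in the documents.
- MVPA spread evenly over waking hours. Assumed, for simplicity.

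**Step 1: least waking time in a valid day.** If the monitor is worn for the whole night, the further hours needed are 10 − s, and the share of the waking day observed is c = (10 − s)/(24 − s).
- s = 7: 3 hours, 3/17 = 17.6%
- s = 8: 2 hours, 2/16 = 12.5%
- s = 9: 1 hour, 1/15 = 6.7%

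**Step 2: effect on mean daily MVPA.** The observed mean is 1 − f × (1 − c) of the true mean. With s = 8, 1 − c = 0.875:
- f = 5%: 1 − 0.05 × 0.875 = 0.956, understated by about 4%
- f = 10%: 0.912, about 9%
- f = 20%: 0.825, about 17.5%
- f = 30%: 0.738, about 26%

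At f = 30% the factor is 0.753 for s = 7 and 0.720 for s = 9, so the share of affected days matters far more than the assumed sleep length.

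**Step 3: the same with ten waking hours required.** The least share of the waking day becomes 10/(24 − s): 10/17 = 59%, 10/16 = 62.5%, 10/15 = 67%. With s = 8 and every affected day at this new minimum, f = 30% gives 1 − 0.30 × (1 − 0.625) = 0.8875, an understatement of about 11% instead of 26%. Some understatement remains, so waking wear time should also enter the adjustment.

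**GPS.** No comparable figure can be computed. The documents do not say how often units were left behind, whether such units logged ten hours, or whether days are averaged or pooled into one ellipse or path.

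**The case against.** The best defence is that the article is a condensed account. It cites a source for the threshold and does not say how wear is scored. The device also yields sleep periods, and the full protocol may remove them before counting hours. That stands as a possibility, and if it is so, one added clause settles the matter. It does not rescue the printed definition, which sets a number of hours without saying waking under a day-and-night wear instruction.

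It is also fair that a thinly observed day requires a woman to keep the monitor on overnight and take it off for most of the day, against instruction. The Compliance section adds daily follow-up of every participant on device issues. These steps should make such days less common, but they do not change which days count as valid.

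Four stronger readings are tempting, and the documents do not support them.

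- That a night's sleep alone qualifies a day. It does so only at ten hours or more; a night of 7 to 9 hours needs 3 to 1 more.
- That bias in PA is shown. It is a risk: the share of affected days is unknown, and nothing indicates that it differs by ward.
- That the feasibility test showed left-at-home GPS units passing as valid days. It reports forgotten units, not that they logged ten hours or were counted. An uncharged unit may not reach ten hours. Read literally, an unworn unit has no wear time.
- That the area ratios in Table 5 (20.48/0.13, about 158-fold at 200 m; 123.02/2.01, about 61-fold at 800 m) measure the exposure error. The exposures are deprivation, disorder, crime and food environment, not area, and the areas are not said to be for single days. With pooled days the effect would be different.

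**Conclusion.** The point holds for the accelerometer. As printed, the rule accepts a day on which only about 7% to 18% of waking time was observed, assuming 7 to 9 hours of sleep with the monitor on. Such days can understate the PA measures used as covariate, moderator and split variable. With 8 hours of sleep and MVPA even over waking hours, the understatement runs from about 4% if 5% of valid days are at the minimum to about 26% if 30% are. These shares are illustrations, not estimates.

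The GPS part is secondary: the definition leaves open how wear is judged for a unit carried in a bag, and the authors' own test shows that units were sometimes left behind. Its size cannot be given.

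Because this is a pilot meant to inform a larger study, the rule is worth correcting now, before it is carried forward.

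**What to change.** **Accelerometer.** Define a valid day as at least ten hours of waking wear, after removing the sleep periods scored from the same device. Adjust PA and sedentary time for waking wear time, as a covariate or by expressing them per waking hour worn. If the full protocol already does this, say so in the definition. The cost is a processing rule on data already collected and somewhat fewer valid days.

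**GPS.** State how wear time is determined for a carried logger. Flag days on which the trace stays at home while EMA location reports or the daily follow-up indicate that the participant was elsewhere, and exclude these days in a sensitivity analysis.

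- Detection will be incomplete. In Table 3 the location items belong to the self-initiated EMA entries, so a question in the daily contact on whether the unit was carried would help.
- Two simpler rules should be avoided. Requiring GPS fixes to coincide with waking accelerometer wear would not detect a logger left at home while the wrist monitor is worn elsewhere. Deleting every home spell with ambulation would remove genuine activity at home.
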